# Effectiveness of shoulder symptom modification approaches in managing patients with frozen shoulder: study protocol for a randomized sham-controlled trial

**DOI:** 10.1186/s13063-026-09661-z

**Published:** 2026-04-16

**Keywords:** Frozen shoulder, Adhesive capsulitis, Symptom modification, Manual therapy, Mobilization with movement, Sham mobilization, NPRS, SPADI, Range of motion

## Abstract

**Background:**

Symptom modification approaches in musculoskeletal physiotherapy practice reduce pain and enhance movement. In our study two symptom modification approaches, shoulder symptom modification procedure (SSMP) and mobilization with movement (MWM) along with sham mobilization are compared. This study aimed to compare the effectiveness of the above approaches in managing pain and shoulder disability and improving shoulder movement in patients with frozen shoulder.

**Methods:**

A total of 36 patients with frozen shoulder, will be randomly allocated for 8 weeks into three groups: (a) the SSMP group (n = 12) (b) the mobilization with movement (MWM) group(n = 12) and (c) sham mobilization group (n = 12). Patients with frozen shoulder aged 40–65 and meeting the inclusion criteria will be eligible. Each group will receive 3 sessions in a week for 8 weeks along with different exercises including isometric, eccentric and concentric followed by the functional program. Measurements will occur at four time points: before the initiation of treatment sessions (week 0), followed by 12 treatment sessions (week 4), then 18 treatment sessions (week 6) and two months from the beginning of the trial (week 8). The primary outcome was functional disability (SPADI). Secondary outcomes included pain intensity (NPRS), active shoulder range of motion (ROM), and the Patient Global Impression of Change (PGIC).

**Discussion:**

This pilot study is the first to examine the effectiveness of symptom-modification approaches in patients with frozen shoulder. The study aims to provide preliminary data on feasibility, safety, and early clinical outcomes, as well as to document challenges encountered during implementation. Findings from this investigation will inform the design, methodology, and sample size estimation for a future large-scale randomized controlled trial assessing the efficacy of symptom-modification interventions in this population.

**Trial registration:**

Clinical Trials.gov NCT06763601. Registered on 12/11/2024. URL of trial registry record: https://register.clinicaltrials.gov/prs/beta/studies/S000F7NU00000067/recordSummary.

**Supplementary Information:**

The online version contains supplementary material available at 10.1186/s13063-026-09661-z.

## Background

Frozen shoulder is a common disorder of the shoulder, which is characterized by shoulder pain, stiffness, and limited active and passive range of motion. This is an inflammatory condition with pain and limitation of mobility that could lead to atrophy of the shoulder muscles resulting from disuse [1], commonly known as frozen shoulder, adhesive capsulitis, and later termed periarthritis by Codman [2].

Globally the prevalence of population affected with frozen shoulder is estimated between 2–5%. Frozen shoulder is a common shoulder condition distinguished by shoulder pain, stiffness, and limited active and passive range of motion, manifesting as a progressive loss of glenohumeral movements associated with pain symptoms [3] must have been stabilized for at least one month or deteriorating, persisting for several months up to two years [4]. Pain and stiffness are the manifestations of progressive fibrosis and contracture of the glenohumeral joint capsule [5]. Frozen shoulder normally develops between the age of 40 and 60 years and is more common among females [6]. In the field of physiotherapy, various treatment approaches have been proposed for the management of adhesive capsulitis, including proprioceptive neuromuscular facilitation (PNF), the Spencer technique, Mobilization with Movement (MWM), as well as conservative interventions such as biophysical agents and therapeutic exercises [7–9]. The Shoulder Symptom Modification Procedure (SSMP), introduced by Jeremy Lewis in 2009, is a structured assessment and treatment approach that emphasizes understanding how specific movements influence shoulder symptoms, rather than focusing exclusively on a pathoanatomical diagnosis [10].

As a novel approach in manual therapy, SSMP provides a staged approach of controlled and segmental mobilisations of shoulder complex i.e., thoracic, scapula and humeral head procedures incorporated with functional movements. This approach aims to modify shoulder arthrokinematics mechanisms to achieve pain free movement of the shoulder and optimize shoulder function, making it a valuable clinical tool in the management of shoulder disorders.

Similarly, MWM is a symptom modification technique designed to reduce pain and restore joint mobility. It has gained widespread clinical utilization due to its demonstrated efficacy in the treatment of adhesive capsulitis. Notably, a systematic review conducted in 2022 concluded that manual therapy interventions, including MWM, are associated with clinically meaningful benefits for patients presenting with shoulder pain and functional limitations [11].

In contrast, sham mobilization is employed in clinical trials as a placebo control to isolate and assess the true efficacy of active manual therapy techniques [12]. The use of such a control is critical for understanding the specific effects of symptom modification approaches and their role in the rehabilitation of musculoskeletal disorders.

Although MWM has shown promising results in clinical trials compared to sham mobilization, the effectiveness of SSMP in reducing pain and disability and in enhancing quality of life for patients with adhesive capsulitis remains an area requiring further investigation. The present trial aims to evaluate the potential benefits of SSMP as a targeted, non-invasive intervention for the management of adhesive capsulitis and to compare its outcomes with those of MWM and sham mobilization.

## Objective

The primary objective of this study was to evaluate the effectiveness of SSMP compared with Mobilization with Movement (MWM) and sham mobilization in patients with frozen shoulder for improving functional disability, reducing pain, and improving range of motion.

## Methods

### Study design

The present RCT is a pilot feasibility study, conducted in accordance with the CONSORT statement. This RCT followed the SPIRIT. (Standard Protocol Items: Recommendations for Interventional Trials) statement [13]. The completed SPIRIT checklist table and figure of the study are added in Annexure. The study flowchart is shown in Fig. 1.

**Fig. 1 Fig1:**
[figure not shown]
Flow chart of the trial in accordance with the SPIRIT statement

### Setting

The study will be taking patients reporting shoulder pain and diagnosed with adhesive capsulitis in Thumbay Physical Therapy and Rehabilitation Hospital. Ajman and Thumbay Hospital, Ajman in the physiotherapy department, UAE.

### Recruitment

The participants will be recruited from Thumbay Physical Therapy and Rehabilitation Hospital and physiotherapy department of Thumbay Hospital, Ajman and physiotherapy department of Thumbay Hospital Ajman. All participants that will be patients diagnosed with adhesive capsulitis by the orthopaedic physician and referred to the physiotherapy department of the hospital will be considered. The Primary investigator and the two therapists in the same hospital will implement the techniques SSMP, MWM and sham mobilization on patients. All participants will read and sign the consent form. The consent declaration will address the protection of personal data and the rights of participants. Volunteers will be informed about: (a) the purpose, procedures, and specifics of the study, (b) their participation being entirely voluntary, and (c) their ongoing right to withdraw from the study at any time, even after providing written consent.

### Randomization and blinding

Sequence generation will be conducted by a biostatistician and allocation concealment managed by a site coordinator, both of whom are independent of recruitment and treatment delivery. Treating physiotherapists are blinded to group allocation during baseline assessment, and outcome assessment will be performed by a blinded assessor.

The hospital provides dedicated administrative and logistical support through a separate wing, allowing the PI to supervise compliance and protocol adherence without influencing randomization or treatment allocation, ensuring methodological integrity. The primary investigator (PI) will oversee the allocation process but will not participate in patient screening, allocation or treatment delivery, in order to minimize potential selection and performance bias.

### Eligibility

The study population will be the patients who are diagnosed with frozen shoulder. The inclusion and exclusion criteria for participants is given below.

#### Inclusion criteria

Diagnosis of adhesive capsulitis confirmed by a healthcare professional.Scores between 2 and 6 in adhesive capsulitis (AC) scale [14].Range of motion affected in capsular pattern.Age between 40–65 years.Willingness to participate by signing informed consent.

#### Exclusion criteria

Having any history of shoulder dislocationHumerus fractures or traumaHaving history of cervical radiculopathyDiagnosed with any sort of cancerHistory of cardiovascular diseaseUse of glucocorticoid injections

### Intervention

Eligible participants will be randomly assigned to one of three groups: the SSMP (group A), MWM (group B), and Sham Intervention (group C). Each participant will undergo baseline assessment, and after assessment, they will be randomised and allocated into one of the three groups and will receive a four-phase designed specific rehabilitation procedures over an 8-week, followed by a follow-up session to assess improvements.

#### Phase 1—Symptom modification approaches and sham mobilization

After the assessment and allocation in Group A, patient identified concerned (PIC) movement will be observed that includes the most painful movement and then targeted SSMP techniques (thoracic repositioning, scapular facilitation, humeral head mobilization, and neuromodulation) will be introduced based on individual’s PIC movement [10, 15].

Participants in Group B will commence mobilization with movement strategies focusing on restoring active and passive range of motion. MWM technique will be carried out based on PIC movement either in flexion, abduction, external and internal rotation directions. MWM technique will be implemented in 3 sequences of 10 repetitions with a rest interval of 30 s between each sequence [16]. Group C will receive a sham mobilization with movement consisting of hand placements mimicking therapeutic positioning, without applying therapeutic force and will be asked to perform the PIC movement up to the pain free range and the dosage will be the same as that of group B. Placebo is not just a comparison intervention, but also acts as an active mechanism that could partly explain the treatment effects seen with manual therapy [17].

#### Phase II – Isometrics

In this phase all the participants in each group will perform isometric exercises using a metronome set at 1 beat per second with a 3 s hold followed by a 3 s rest, of 4 repetitions.

#### Phase III—Eccentrics and Heavy Slow Resistance exercises

This phase includes eccentric exercises initially performed on the unaffected and then affected by choosing the most painful movement, using a 5 s contraction guided by a metronome. Participants will be made to perform three sets of five repetitions with gradually progression to heavy slow resistance exercise.

Heavy slow resistance (HSR)- the HSR program is a combination of eccentric and concentric loading. One repetition maximum was determined for the concentric loading. Exercise will be performed using a metronome of 3 beats for the eccentric phase as well as 3 beats for the concentric phase, making the eccentric-concentric contraction total 6 seconds per repetition, beginning at 70% of 1 repetition maximum (1RM) and progressing up to 85% of 1RM, with one set of five repetitions.

#### Phase IV—Functional programme

This phase will include five functional exercises, such as wall push-ups and upper limb weight-shifting exercises (as illustrated in Fig. 2). The aim is to restore functional movement patterns relevant to daily activities.

**Fig. 2 Fig2:**
[figure not shown]
Exercises of functional program

Transcutaneous Electrical Nerve Stimulation (TENS) will be permitted as a standardized rescue analgesic intervention during the first two weeks only if a participant reported an NPRS score equal to or higher than the previous session. The TENS parameters (frequency, pulse duration, intensity, and treatment duration) will be standardized across all groups to ensure uniform exposure. The frequency of TENS usage shall be documented and later incorporated into statistical analysis as a covariate to minimize any confounding effects. TENS The frequency of TENS application will be recorded across all groups.

### Outcome measures

The evaluations will take place at four time points: prior to treatment (week 0), post-treatment (week 4 and 6), and two months subsequent at week 8. The primary outcome of this study was functional disability as measured by the Shoulder Pain and Disability Index (SPADI). In addition, the secondary outcomes included pain intensity measured using the Numeric Pain Rating Scale (NPRS), active shoulder range of motion (ROM), and the Patient Global Impression of Change (PGIC).

#### Primary outcome measures

Shoulder pain and disability index (SPADI)- The internal consistency of the SPADI was satisfactory for pain (α = 0.859) and disability (α = 0.895). Moreover, a high test–retest reliability value was found for ICC for pain = 0.989 [95% CI = 0.975–0.995]; ICC for disability = 0.990 [95% CI = 0.988–0.998] [18].

#### Secondary outcome measures

Numeric pain rating scale(NPRS)—The test–retest reliability of the NPRS for literate and illiterate rheumatoid arthritis patients is 0.96 and 0.95, respectively. Construct validity of the NPRS by correlation with VAS has a range of 0.86 to 0.95, showing that this measure possesses a high degree of reliability and validity for the measurement of pain intensity [19].

##### Joint range of motion

D WALL to measure shoulder joint ROM. The D-wall platform uses a 3D camera to monitor the joint angles and range of motion. In addition, it provides a reliable measurement and accurate angles. The D-Wall Techno Body is equipped with sensors that are placed at specific points on the body. These sensors tracked the movements of the joints being evaluated. As the user moves the joint through its full range of motion, the sensors capture the data and transmit it to the device software [20].

Evidence supports the validity and reliability of the TecnoBody D-Wall and Kinovea systems for assessing joint ROM during functional movements, with ICC values exceeding 0.90, indicating excellent agreement. The D-Wall system’s 3D motion capture capabilities and real-time biofeedback allow clinicians to track movement patterns accurately, even in complex or multi-joint motions, which can help mitigate errors caused by compensatory movements [21]. To enhance measurement reliability in patients with capsular restriction patterns characteristic of frozen shoulder, a standardized calibration protocol will be performed prior to each assessment session. Participants are instructed to minimize compensatory scapular elevation, and assessor-guided stabilization will be applied when required.

##### Patient Global Impression of Change Scale(PGICS)

The PGICS is a single-item rating scale that has emerged as a reliable and interpretable single-item rating of global improvement in clinical trials for chronic pain. Respondents rate their overall change in condition on a 7-point Likert scale ranging from "very much improved" to "very much worse." Owing to its ease of administration and capacity to capture patient-reported outcomes, the PGICS has provided valuable insights into recent research involving chronic pain [22].

### Anticipated dates of trial commencement and completion

The study started in January 2025 and is scheduled to be completed by July 2026.

### Sample size calculation

As the study is a pilot study, the sample size will depend on the number of patients outflow to the Thumbay Hospital and rehabilitation hospital, Ajman. As for estimated we have decided 12 patients in each group as a thumb rule of pilot study [23].

### Data collection and management

Outcome data will be systematically collected by the primary investigator before and after intervention. These data will be carefully analysed to assess the effects of the intervention. The study will be closely supervised by a professor of physiotherapy who will oversee the data collection process conducted by the primary investigator. To promote participant compliance, timely text message reminders with relevant information about upcoming appointment sessions will be sent to their mobile phones. Regarding data management, all research-related data will be stored securely in a protected database to ensure confidentiality and integrity. Hard copies of the signed informed consent forms will be maintained within the study facility. Monthly backups of all digital data entries will be created and maintained throughout the trial. At the conclusion of the study, the final Excel spreadsheet will be submitted to a statistician for data analysis.

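### The protocol contradicts itself on whether the primary investigator treats and collects outcomes, so its claim of blinded assessment cannot be relied on

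*Protocol article*

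**What the plan says.** Three sections of Methods in the protocol article describe what the PI does.

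- **Recruitment**, on delivery: "The Primary investigator and the two therapists in the same hospital will implement the techniques SSMP, MWM and sham mobilization on patients".
- **Randomization and blinding**, on the PI: the PI "will oversee the allocation process but will not participate in patient screening, allocation or treatment delivery". The stated reason is to limit selection and performance bias. The section also describes hospital support "allowing the PI to supervise compliance and protocol adherence without influencing randomization or treatment allocation". On measurement it says that "outcome assessment will be performed by a blinded assessor".
- **Data collection and management**: "Outcome data will be systematically collected by the primary investigator before and after intervention". The next mention is of a supervising professor "who will oversee the data collection process conducted by the primary investigator". The blinded assessor does not appear in this section.

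The PI is nowhere described as blinded. The Intervention section places randomisation after the baseline assessment.

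**The concern.** Two statements of role conflict. One section has the PI applying the techniques and another rules that out. One section gives outcome assessment to a blinded assessor and another gives outcome collection to the PI. A person who applies SSMP, MWM or sham to a participant knows that participant's arm, so a treating PI cannot be the blinded assessor for that participant.

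Blinded assessment carries weight in this trial. The Discussion says the sham arm is there to separate specific effects from contextual ones. SPADI, NPRS and PGIC are self-reported, and answers given to one's own therapist may differ from answers given to a neutral assessor. ROM depends partly on the assessor, since the Joint range of motion section allows the assessor to stabilise the participant as needed. Under Statistical analysis, the main products are effect sizes and confidence intervals for planning a definitive trial. A systematic shift between arms would pass into those estimates, and a wide interval would not reveal it.

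**Working it through.** **Comparison of the text.** The plan gives no figure on this point to reproduce, so the check is a side-by-side reading.

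| Question | Recruitment | Randomization and blinding | Data collection and management |
|---|---|---|---|
| Does the PI treat? | Yes, with two therapists | No | Not addressed |
| Who measures or collects outcomes? | Not addressed | A blinded assessor | The PI, stated twice |
| Does the PI know the arm? | Yes, for those the PI treats | Oversees allocation and supervises adherence; not described as blinded | Not addressed |

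1. *Treatment delivery.* The first row is an outright contradiction: the same role both delivers the techniques and takes no part in delivery.
2. *Outcome measurement.* The second row conflicts on its ordinary reading. Collection before and after the intervention describes what happens at visits, and storage, backups and the final spreadsheet are covered separately.
3. *Combined effect.* Following Recruitment and Data collection together, one person may both treat a participant and collect that participant's outcomes.
4. *Visits exposed.* Assessments are at weeks 0, 4, 6 and 8. Week 0 comes before randomisation, so nobody can know the arm then. Exposure is confined to weeks 4, 6 and 8.

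**Illustration of scale.** The only input from the documents is 12 participants per group (Sample size calculation). The shift b between two arms is an assumption, taken here as 0.2 to 0.4 SD and present at every assessment in the contrast.

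- Standard error of a difference between two arm means, in SD units: sqrt(1/12 + 1/12) = sqrt(2/12) = 0.408.
- Two-sided error at nominal 5% when there is no true difference: P(|Z + b/0.408| > 1.96).
- b = 0.2: b/0.408 = 0.49, giving P(Z > 1.47) + P(Z < -2.45) = 0.071 + 0.007 = 0.078.
- b = 0.4: b/0.408 = 0.98, giving P(Z > 0.98) + P(Z < -2.94) = 0.163 + 0.002 = 0.165.
- With a t test on 12 + 12 - 2 = 22 degrees of freedom (critical value 2.074, noncentral t), the same shifts give 0.076 and 0.155.

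The illustrative range is therefore about 8% to 16%. The contradiction does not depend on it.

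**The case against.** The strongest reply is that Randomization and blinding is the section written to govern this matter. On that view it should prevail, and the PI's collection of data under a heading that includes data management means compiling what the blinded assessor has measured. This is a possible reading. It is not the natural one, because the text refers to collection before and after the intervention and to a data collection process that the PI conducts. It also leaves the conflict over treatment delivery untouched.

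Several limits do stand:

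- A reader might infer that the trial has no blinded assessment at all. The documents do not support that. They never say which section is followed in practice, only that the claim is contradicted.
- A reader might infer that the PI personally administers every questionnaire and measures every ROM. Data collection and management says neither this nor that the PI collects all outcome data.
- A reader might infer that the PI knows every participant's arm. Under Recruitment the PI is one of three people delivering treatment, so knowledge follows directly only for those the PI treats. For the others it is plausible, given oversight of allocation and adherence, but it is not stated. Overseeing allocation without taking part in it is not in itself a contradiction.
- A reader might infer that any bias favours SSMP as the newer technique. No section gives a direction.
- Type I error is not the main measure for a pilot centred on estimation, and the full assumed shift would reach the effect estimate only if all the assessments entering the contrast were affected.

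**Conclusion.** The contradiction is real and should be corrected before results are reported. It lies in what the article states, so it is not a detail left to a fuller protocol. The conflict over treatment delivery is outright. The conflict over outcome collection rests on the ordinary reading of the data collection section.

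The supportable conclusion is that blinded assessment at weeks 4, 6 and 8 is contradicted and cannot be relied on as written. Whether unblinded assessment has taken place, and for how many participants, cannot be told from the document. The 8% to 16% range rests wholly on the assumed 0.2 to 0.4 SD shift and is not an estimate of bias in this trial. Pilot status does not remove the problem, because the effect sizes are meant to inform the sample size of the next trial.

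**What to change.** 1. Reconcile Recruitment, Randomization and blinding, and Data collection and management. State that SPADI, NPRS, ROM and PGIC at every post-baseline visit are collected by the blinded assessor already named, who neither treats participants nor oversees allocation.
2. In Data collection and management, limit the PI to compiling and managing the data.
3. State one consistent PI role in treatment delivery and use it in all three sections.
4. As the study status is recruiting, record who treated and who assessed each participant at each visit, including visits already held where this can be established.
5. Report, by arm, how many post-baseline assessments were made by someone aware of allocation, and claim blinded assessment only for the rest.

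Repeating the SPADI analysis without the affected visits is not recommended. If the PI collected everything, no post-baseline data would remain. If only some visits were affected, the exclusion would be non-random in arms of 12.

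The cost is revised wording and a treater/assessor field on the case record. The plan already names the assessor role, so no new role is needed. The document does not show that the role is filled by someone other than the PI and the therapists, and the sponsor should confirm this.
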